### Defintion of a serious adverse event

A serious adverse event (experience) (SAE) or reaction is any untoward medical occurrence that at any dose :

- results in death;
- is life-threatening;
- requires hospitalization (other than for drug administration) or prolongation of existing hospitalization;
- results in persistent or significant disability/incapacity; or
- is a congenital anomaly/birth defect.

And also

- other important medical events (jeopardise the subject or require intervention to prevent one of the other outcomes listed in the definition above).

**All serious adverse events, whether or not deemed drug-related, or expected, must be reported immediately or within 24 hours (one working day), using the Serious Adverse Event Notification Form , by telefax to :**

### Reporting of adverse events

For all adverse events identified, an adverse event report form will be completed.

For each possible adverse event identified and considered as **serious**, a serious adverse event notification form will be completed.

The following information will be recorded for all adverse events:

1. Description of event
2. Date of event onset
3. Date event reported
4. Severity of the event
5. Relationship of the event to study medication
6. Is the event serious ?
7. Initials of the person reporting the event
8. Was the event episodic or intermittent in nature ?
9. Outcome of adverse event
10. Action taken
11. Date event resolved.

A severity grading scale, based on toxicity grading scales developed by the WHO and the National Institutes of Health, Division of Microbiology and Infectious Diseases, will be used to grade severity of all symptoms, physical exam findings, and haemoglobin results (see Appendix I). Any new event, or an event present at baseline that is increasing in severity, will be considered as an adverse event.

## Laboratory Evaluations

Blood samples will be properly labelled with patients' initials, randomisation number, protocol number, the study day and the date the sample is taken. Haematology and Clinical chemistry assessments will be performed locally at sites. Blood samples for clinical chemistry tests will be sent to MDS Pharma Services central laboratory.

All laboratory results will be reported in Standard International Units or in conventional units.

For laboratory analysis, a total volume of blood of about 2 ml x 4 times will be drawn from each child throughout the study. **Sites may draw blood via venopuncture or finger prick.**

*Haematology and Blood Chemistry Tests*

Haemoglobin, , red blood cells count, total white blood cell count, differential count, platelet count, total bilirubin, ALAT, creatinine.

**Sample management in CISM.**

1. **All samples taken from the study participants will be drawn from capillary finger pricking.**
2. **At each participant visit, one drop of blood will be taken for blood slides and in most of the visits for filter paper too.**
3. **For laboratory analysis, a total volume of blood of about 2mL x 4 times will be drawn from each child throughout the study.**
4. **Should any participant become ill during the study, they will be seen at Manhiça’s Hospital outpatients department, where they shall be managed according to the usual procedures. In that case, and only whenever a positive parasitaemia has been detected, an extra blood sample will be taken for filter paper and haematology determination.**
5. **Haematology and biochemistry assessments, as well as blood slide reading for malaria diagnosis will be performed on site.**
6. **Filter paper for *P.falciparum*’s PCR detection and genotyping will be sent to Antwerp (Belgium) where it will be analysed and stored.**
7. **Blood slides will be kept and stored on site until a certain amount is sent for quality control survey to the reference laboratory:**

***Abnormal Laboratory Test Results***

The Investigator will mark in the CRF the laboratory values out of normal ranges and will indicate those of clinical importance. These will be considered as AEs, and the proper AE reporting procedure should be followed by the Investigator.

## Vital Signs

For a comprehensive safety and tolerability evaluation of the study drug, vital signs (systolic and diastolic blood pressure, heart rate) will be recorded at each visit of the study.

The Investigator should mark in the CRF the heart rate and arterial pressure values out of normal ranges and indicate those of clinical importance. These will be considered as AEs, and the proper AE reporting procedure will be followed by the Investigator.

# CASE REPORT FORM (CRF)

Presentation of the CRF

The CRF to be used for the study consists of pages headed with the study code and other relevant information. It is composed of an introductive part for the selection and inclusion of patients in the study and special forms for the different evaluation times; at the end of the CRF are the forms for registration of possible adverse events and for any suspension of the study. Each page includes a header containing information for the identification on the study subject (Study number and Initials; to be completed by the Investigator) and the study code.

How to use the CRF

It is recommended that the CRF be filled out using a ballpoint pen with black ink.

All requested information must be entered on the CRFs. If an item is not available or is not applicable, this fact should be indicated; there should be no blank spaces. A correction should be made by striking through the incorrect entry with a single line and by entering the correct information adjacent to it. The correction must be initialled, dated and explained if necessary by the Investigator or by a qualified individual specifically designated by the Investigator. Each completed Case Report Form must be reviewed, signed and dated by the Investigator.

# STATISTICS

The statistical analysis will be performed by MDS Pharma Services and detailed in the statistical analysis plan (SAP) that will be prepared within the first month of study initiation.

## Population Analysed

The following populations will be considered for the statistical analysis of efficacy.

**Intention-to-Treat (ITT) Population**. Defined as all randomized patients who will take at least one dose of the study treatment. All patients who withdrew from the study for one of the reasons listed in section 5 as well as the patients for whom the PCR is not interpretable or missing will be evaluated as failures. For the robustness analyses, these patients will be evaluated in different ways in this population (see section 9.2).

**Modified Intention-to-Treat (modified ITT) Population**. Defined as the ITT population with the exclusion of the lost-to-follow-up patients before Day 28 for unknown reasons (non informative drop-outs). More specifically, patients withdrawing from the study for reason 7 (see section 5) will be excluded, while all other withdrawals will be counted as failures (these reasons might be potentially considered correlated with lack of efficacy, i.e. are referred to as informative drop-outs). The patients for whom the PCR is not interpretable or missing will be assigned the result “recrudescence” or “re-infection” according to the ratio between these outcomes which was observed among the evaluable PCRs within each treatment group. This rule about PCR will be applied for the primary analysis. For all analyses for which the knowledge of the outcome is needed for each patient individually (for example, the Breslow Day test or the logistic regression or the analyses where a baseline covariate is needed), different scenarios will be considered, i.e. the most two extreme ones of considering all patients with not interpretable or missing PCRs as failures or as successes and the intermediate one of excluding them all.

**Per-Protocol (PP) Population**: defined as all randomized patients who will be eligible according to the study protocol, will receive at least 80% of the study medication, will have the Day 28 assessment, will not take other anti-malarial drugs and, in case of the presence of asexual parasite stages on thick or thin blood smears, will have an evaluable PCR. The protocol violations listed below will also be considered reasons for excluding the patients from this population:

 failure to attend a follow-up visit on Days 0-2 and patient cannot be located within 6 hours of scheduled time;

 failure to attend two consecutive follow-up visits from Day 3 to Day 28 (visits from Day 3 to 28 must take place within 24 hours of the scheduled time and from Days 14 to 28 within 48 hours of the scheduled time).

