## Primary Objective

The primary objective of the study is to measure the Day 28, PCR corrected cure rates of Artekin and Coartem and demonstrate that the cure rate of the former treatment is non-inferior to that of the latter (non-inferiority margin = 5%). This cure rate is defined as the proportion of patients with adequate clinical and parasitological response at Day 28 plus those treatment failures identified as new infection by PCR.

In order to compare the study results with the historical ones, the criteria described in the WHO document (“Assessment and Monitoring of Antimalarial Drug Efficacy for the Treatment of Uncomplicated Falciparum Malaria – 2003”. See chapter 7, section 7.3) will be used, i.e. the failure rates computed in each treatment group individually considered will be judged against the efficacy threshold of 90%.

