## Primary Endpoint

The primary endpoint will be the PCR-corrected adequate clinical and parasitological response (PCR corrected ACPR) at D28.

ACPR is defined as the absence of parasitaemia on D28 irrespective of the axillary temperature without previously meeting any of the criteria of early treatment failure or late clinical or parasitological failure.

Patients with late asexual parasite reappearance will be considered ACPR if the PCR analysis shows a new infection rather than a recrudescence.

The total treatment failure is defined according to the WHO criteria (WHO 2003) as the sum of early* and late** treatment failures.

* Early Treatment Failure (ETF)

*(i) Development of danger signs or severe malaria on Day 0, Day 1, Day 2 or Day 3, in the presence of parasitaemia,*

*(ii) Parasite density on Day 2 > Day 0 count irrespective of axillary temperature,*

*(iii) Presence of parasitaemia on Day 3 with fever (axillary temperature ≥ 37.5°C),*

*(iv) Parasitaemia on Day 3 ≥ 25 % of count on Day 0.*

** Late treatment failure (LTF)

Late Clinical Failure (LCF)*:*

*(i) Development of danger signs or severe malaria after Day 3 in the presence of parasitaemia, (See Appendix V for the critera for severe malaria/danger signs)*

*(ii) Presence of parasitaemia and fever on any day from Day 4 to Day 28, without previously meeting the criteria of ETF.*

Late Parasitological Failure (LPF)*:*

*Reappearance of parasitaemia after initial clearance between day 4 and day 28 (identified as recrudescent infection by PCR analysis) in the absence of fever (axillary temperature <37.5°C) without previously meeting the criteria of ETF or LCF.*

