# PATIENT WITHDRAWAL CRITERIA

During the study, the following conditions are reasons **for stopping the study treatment and/or for excluding the patients from further efficacy assessments:**

1. Any treatment failure (including early failures);

2. Withdrawal of informed consent;

3. Use of antimalarial drugs (or antibiotics with antimalarial activity) outside of the study protocol;

4. Persistent vomiting of study drugs **on Day 0**  (at least twice the same dose);

5. Failure to complete the study treatment

6. Investigator's request for safety reasons (for example, onset of serious adverse events, necessitating study interruption);

6. Lost to follow-up (unable to locate the patient) before Day 28.

Patients with one or more of the conditions listed above will have to be followed-up for the safety assessment until Day 42

These reasons for premature withdrawing will be referred to Day 28 (primary evaluation time).

The reasons for withdrawing between Day 29 and Day 42 will also be recorded in the study CRF.

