## Efficacy

9.2.1 Analysis for showing non-inferiority of Artekin vs Coartem

The primary analysis will be based on a 97.5% (one-sided) Confidence Interval (CI) computed on the difference between the 28-day PCR corrected cure rates of the test and the reference treatments, respectively.

In order to claim that Artekin is non-inferior to Coartem the lower limit of the CI must be > -0.05 in both the modified ITT and the Per Protocol populations. The analysis on the more pure ITT population (see section 9.1) will be used for investigating robustness of results (see below).

The method for computing the CI will be specified in the SAP.

For computing the PCR-corrected cure rate, the patients who are diagnosed to be re-infected will be counted as successes (they have to be terminated on that day of follow-up) while the patients for whom the PCR is not interpretable or the sample is unavailable will be treated differently depending on the population considered (see section 9.1).

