9.2.2 Historical comparisons

In order to compare the study results with the historical ones, the criteria described in the WHO document (“Assessment and Monitoring of Antimalarial Drug Efficacy for the Treatment of Uncomplicated Falciparum Malaria – 2003”. See chapter 7, section 7.3) will be used. Therefore, the failure rates will be estimated through survival analysis (Kaplan-Meier method) in each treatment group individually considered. This analysis will be carried-out in the per-protocol population and the results obtained in each of the two treatment groups will be judged against the threshold of 90% (there is consensus among the malaria experts in recognising that the threshold of 90% should be considered as a “rule of thumb” for judging efficacy)..

Robust analysis will be performed on the more pure ITT population by applying the following methods:

1. All patients who withdrew from the study for one of the reasons listed above (from 1 to **7**) will be evaluated as failures.

2. Patients who withdrew from the study for reasons that cannot be considered uncorrelated with the study treatments (i.e. reasons from 1 to **6**) will be counted as failures (i.e. assigned with a 0 value), while the patients prematurely interrupting the study for reason **7** will be assigned with a value ranging from 0.5 to 0.9 (imputation of a postulated probability of success for the patients for whom the treatment outcome could not be evaluated). Finally, all cured patients will be assigned with a 1 and this transformed endpoint will be summarized in terms of means and corresponding standard errors by treatment group.

3. The analysis of the 28-day PCR corrected cure rates will be performed by means of the survival analysis techniques, where the non informative lost-to-follow-up patients (i.e. patients withdrawing for unknown reasons) will be censored at the time of exiting the study.

The impact of these strategies on the conclusions will be carefully evaluated and discussed

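### The rules that score withdrawals as failures make no exception for PCR-confirmed new infections, which the primary endpoint counts as cures

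*Combined protocol and SAP*

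**What the plan says.** **Rules that make the child a failure**

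- Section 5 lists as withdrawal reason 1: "Any treatment failure (including early failures". It has no PCR qualifier.
- Section 9.1, ITT: those described as "All patients who withdrew from the study for one of the reasons listed in section 5" are evaluated as failures.
- Section 9.1, modified ITT: "patients withdrawing from the study for reason 7 (see section 5) will be excluded, while all other withdrawals will be counted as failures". Section 5 prints two items numbered 6, so reason 7 is the seventh item, loss to follow-up.
- Section 9.2.2, method 1, starts from "All patients who withdrew from the study for one of the reasons listed above" and scores reasons 1 to 7 as failures. Method 2 gives 0 for reasons 1 to 6, a value between 0.5 and 0.9 for reason 7, and 1 for cured children.

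**Rules that make the same child a success**

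- Section 2.1 defines cure as "adequate clinical and parasitological response at Day 28 plus those treatment failures identified as new infection by PCR".
- Section 3.2: "Patients with late asexual parasite reappearance will be considered ACPR if the PCR analysis shows a new infection rather than a recrudescence".
- Section 9.2.1: "the patients who are diagnosed to be re-infected will be counted as successes (they have to be terminated on that day of follow-up".

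Section 9.2.1 lets only uninterpretable or unavailable PCR results vary by population, and refers to section 9.1 for them.

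**The concern.** The two sets of rules meet in one child: a recurrence from Day 4 leads to withdrawal, and PCR later shows a new infection. The case is clearest when the child is febrile. Late clinical failure in section 3.2 requires only parasitaemia and fever between Day 4 and Day 28, with no PCR condition. Section 4.4 withdraws clinical failures. Section 3.8 genotypes samples from children already classified as late treatment failures, so the label comes before the PCR result. Section 2.1 itself calls new infections treatment failures.

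For afebrile recurrences the text is mixed. Section 3.2 restricts late parasitological failure to recrudescence, but Appendix VIII defines it at Day 28 or Day 42 without a PCR condition.

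At stake is the coding of a co-primary population and of its robustness analyses in an open-label trial. If the withdrawal rule were programmed as written, new infections would enter the failure count of a rate called PCR-corrected. That costs power. If re-infection differs between arms, it also moves the estimated difference for reasons unrelated to recrudescence. In method 2 the same child would score 0 as a reason-1 withdrawal and 1 as a cured child.

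**Working it through.** **Inputs from section 3.4.1.** One-sided alpha 0.025; margin -0.05; 1000 and 500 randomised. Modified ITT attrition is 10%, leaving 900 and 450, with cure 91%. Per Protocol attrition is 30%, leaving 700 and 350, with cure 93%.

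**Assumed input.** The documents give no re-infection rates. I use 2%, 5% and 10% of children, written rT (DHA+PPQ) and rR (Coartem).

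**Formula.** Power = Φ((pT - pR + 0.05 - c)/SE - 1.96), with SE = √(pT(1-pT)/nT + pR(1-pR)/nR) and continuity correction c = (1/nT + 1/nR)/2.

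**Step 1: the plan's own figures.**

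- Modified ITT: SE = √(0.91 × 0.09 × (1/900 + 1/450)) = 0.01652 and c = 0.00167. Then (0.05 - 0.00167)/0.01652 - 1.96 = 0.965, so power is 83.3% (stated: about 83%).
- Per Protocol: SE = √(0.93 × 0.07 × (1/700 + 1/350)) = 0.01670 and c = 0.00214. Then (0.05 - 0.00214)/0.01670 - 1.96 = 0.905, so power is 81.7% (stated: 82%).

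Both figures reproduce. They belong to the reading in which re-infection is a success.

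**Step 2: literal rule, equal re-infection.** True corrected cure is 91% in both arms of the modified ITT. The analysed rate is 0.91 - r.

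| Re-infection, both arms | Analysed rate | SE | Power |
| --- | --- | --- | --- |
| 0% | 0.91 | 0.01652 | 83.3% |
| 2% | 0.89 | 0.01807 | 76.3% |
| 5% | 0.86 | 0.02003 | 67.5% |
| 10% | 0.81 | 0.02265 | 56.9% |

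A claim needs both populations, so its probability cannot exceed the modified ITT figure. Per Protocol does not give this loss back.

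**Step 3: literal rule, unequal re-infection.** The analysed difference is (pT - rT) - (pR - rR), so it shifts by rR - rT. With 91% cure in both arms:

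- 5% DHA+PPQ, 2% Coartem: shift -3 points, power 16.3%.
- 5% DHA+PPQ, 10% Coartem: shift +5 points, power 99.5%.

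**Step 4: a true deficit at the margin.** Take cure of 86% and 91%, with re-infection of 5% and 10%. Both analysed rates become 0.81. Without continuity correction, the chance that the modified ITT bound passes is Φ(0.05/0.02265 - 1.96) = 59.8%, against a nominal 2.5%. This is for the modified ITT alone. The chance that both populations pass cannot exceed the Per Protocol chance. If the deficit is also 5 points in Per Protocol, and re-infections are scored there under section 9.2.1, that chance is about 2.5%.

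**The case against.** The strongest reply is that the primary analysis already has the right rule. Section 9.2.1 is written for computing the PCR-corrected cure rate. It foresees that re-infected children leave the study and still counts them as successes. A specific rule ordinarily prevails over a general drop-out rule.

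Section 9.1 points the same way:

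- The modified ITT paragraph splits missing PCR results into recrudescence and re-infection by the observed ratio, which is pointless if both are failures.
- The ITT paragraph lists non-evaluable PCR separately as failure, which would be largely redundant if every recurrence already failed.
- The withdrawal rule is justified by informative drop-out, whereas a recurrence classified by PCR has an observed outcome.

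Most of this stands for the primary modified ITT analysis. It shows intent, but no sentence gives section 9.2.1 precedence over the withdrawal clause in section 9.1. It carries less weight for the pure ITT population and methods 1 and 2, where the success rule is not restated. Method 3 (survival analysis) and the Per Protocol definition contain no such withdrawal rule and are unaffected.

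A reader might infer that the primary analysis is in effect uncorrected for PCR, or that the trial's false-positive risk rises to something like 60%. The documents support neither reading. The first ignores section 9.2.1. The second takes a modified ITT figure under assumed rates that favour the test arm and leaves out the Per Protocol requirement. The synopsis also asks for a DHA+PPQ point estimate above 0.90 in both populations. An analysed rate of 0.81 would almost surely miss that.

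**Conclusion.** The protocol has an unresolved conflict between its withdrawal-equals-failure rules and its PCR-corrected endpoint. It is strongest for the ITT definition and robustness methods 1 and 2. For the primary modified ITT analysis the intended rule can be inferred, but it is not stated which clause governs.

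The size depends on the literal rule being programmed and on assumed re-infection rates. On those terms the main harms are lost modified ITT power (step 2) and robustness analyses distorted by new infections, in a direction set by which arm has more of them. No inflation of the trial's overall type I error is shown. This is more than missing detail, because rules already written would give a wrong result if followed as they stand.

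**What to change.** In section 9.1 (ITT and modified ITT) and section 9.2.2 (methods 1 and 2), and then in the SAP, add wording such as: children withdrawn under reason 1 for a recurrence from Day 4 are classified by PCR as in section 9.2.1, with re-infection a success, recrudescence a failure, and a non-evaluable result handled by the rule of that population. Withdrawal-equals-failure then applies only to early treatment failure and the other informative reasons. Each analysis keeps its present handling of loss to follow-up.

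At the same time, correct the duplicate number 6 in section 5, so that the references to reason 7 point to a printed item.

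The cost is one sentence in each place. No new data are needed. The planned power of about 83% and 82% is unchanged, since it already assumes that re-infection is a success. Section 9 places the SAP within the first month of study initiation, so the coding can be fixed there before outcome data are examined.

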## Rescue Treatments

Patients with clinical treatment failure will be withdrawn from the study, treated, and followed up as per local practice. They will not have study investigations performed thereafter. Patients requiring rescue therapy (ETF, LCF) will be treated by members of the study team with quinine 10 mg/kg orally three times a day for 7 days or any other appropriate oral treatment unrelated to the study drugs. Any patient, who is diagnosed with severe malaria or danger signs during follow-up, will be referred for treatment with parenteral quinine and supportive measures at the local facility or hospital.

Patients with asymptomatic recurrent parasitaemia will also receive rescue therapy.

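### Read literally, the co-primary per-protocol definition drops most children who fail or have a recurrence before Day 28, contrary to the plan's own PP cure rate and power

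*Combined protocol and SAP*

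**What the plan says.** Section 9.1 defines PP as eligible randomised children who receive at least 80% of study medication and who "will have the Day 28 assessment, will not take other anti-malarial drugs". It adds that a child, "in case of the presence of asexual parasite stages on thick or thin blood smears, will have an evaluable PCR". Missing two consecutive visits between Day 3 and Day 28 is a further exclusion. Nothing is said about children who fail treatment or about rescue drugs.

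Other sections say what happens to those children:

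- Section 4.4: "Patients with clinical treatment failure will be withdrawn from the study, treated, and followed up as per local practice", followed by "They will not have study investigations performed thereafter". It also says: "Patients with asymptomatic recurrent parasitaemia will also receive rescue therapy".
- Section 5: any treatment failure is the first listed reason for stopping treatment or ending efficacy assessments. Yet "Patients with one or more of the conditions listed above will have to be followed-up for the safety assessment until Day 42".
- Section 9.2.1: PCR-diagnosed re-infections count as successes, but "they have to be terminated on that day of follow-up".

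PP carries weight in two places. Under section 9.2.1, non-inferiority must be shown in both the modified ITT (mITT) and PP. Under section 9.2.2, Kaplan-Meier failure rates are judged against 90%, and "This analysis will be carried-out in the per-protocol population".

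**The concern.** A child who fails on Day 14, say, is withdrawn and rescued. That child has taken another antimalarial. If followed no further for efficacy, the child also lacks a Day 28 assessment and misses Days 21 and 28, two consecutive visits. The written rule therefore removes the outcome events that the population is meant to measure, and keeps mainly cures plus failures first found at the Day 28 visit. Re-infected children, whom the plan counts as successes, are lost the same way.

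Removing failures raises both arms' cure rates and pulls the difference towards zero, which in a non-inferiority trial favours the claim. A programmer who follows the text and one who follows the evident intent would build different PP sets. In an open-label trial that choice would be made with outcomes already visible, and section 15.1 gives PP exclusions to a Steering Committee that includes investigators.

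**Working it through.** **Inputs from section 3.4.1.** 1000 and 500 children; PP attrition 30%, giving 700/350; expected PP cure rate 93%; mITT attrition 10%, giving 900/450, at 91%; margin -0.05; one-sided alpha 0.025; continuity correction.

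**Step 1: the plan's own power.** Power = Φ[(0.05 − k)/SE − 1.96], with k = ½(1/n_T + 1/n_R) and SE = √[p(1−p)(1/n_T + 1/n_R)].

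- PP: k = 0.00214 and SE = 0.01670. (0.05 − 0.00214)/0.01670 − 1.96 = 0.905, so power is 81.7% (stated 82%).
- mITT: k = 0.00167 and SE = 0.01652, so power is 83.3% (stated approximately 83%).

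Both stated figures reproduce. The PP figure needs the 7% failures to be in the population. If both arms truly cure 93%, the same formula under the literal rule gives 97.0% power when half the failures are retained, and almost 100% when one fifth are. The trial was therefore not sized on the literal definition.

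**Step 2: apparent cure rate under the literal rule.** Let p be the cure rate with all failures kept, and s the share of failures first detected at the Day 28 visit. The documents do not give s; 0.5 to 0.2 is an assumed range. With re-infections left in, the apparent rate is p / [p + (1 − p)s].

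| True rate | s = 0.5 | s = 1/3 | s = 0.2 |
|---|---|---|---|
| 93% | 96.4% | 97.6% | 98.5% |
| 88% | 93.6% | 95.7% | 97.3% |
| 83% | 90.7% | 93.6% | 96.1% |

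Removing re-infections as well (assumed 20% of children, also not in the documents) moves the 93% row to 0.73/(0.73 + 0.07s): 95.4% at s = 0.5 and 98.1% at s = 0.2.

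At a true 88% v 93%, the expected PP difference shrinks from -5.0 points to -2.8 (s = 0.5) or -1.2 (s = 0.2).

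**Step 3: chance of passing when the test arm is exactly at the margin.** Simulation at a true 88% v 93%, with PP 700/350 nested in mITT 900/450 and a continuity-corrected Wald lower bound required to exceed -0.05. Re-infections are left in.

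| Failures retained in PP | PP leg alone passes | Both legs pass |
|---|---|---|
| All | 1.6% | 0.9% |
| s = 0.5 | 30% | 1.6% |
| s = 1/3 | 71% | 1.7% |
| s = 0.2 | 98% | 1.7% |

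**Step 4: the 90% judgement.** If every PP child has a Day 28 assessment, none is censored earlier, so the Kaplan-Meier estimate at Day 28 equals the simple proportion in Step 2. An arm with a true 83% would then appear as about 91% to 96% and clear the threshold.

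**The case against.** **The intent is clear and the text leaves some room.** The evaluable-PCR clause, the 93% expectation and the Kaplan-Meier analysis all presuppose failures in PP. Section 5 limits antimalarial use as a withdrawal reason to use not provided for by the protocol, and rescue is provided for. Section 5 also keeps withdrawn children in safety follow-up, and the ban on later investigations in section 4.4 is attached to clinical failure only. So it is not established that every failing child breaks both PP conditions. This stands as evidence of intent. It does not cure the wording: the limit in section 5 is absent from the PP definition, and a safety visit on Day 28 would not undo the antimalarial exclusion. Section 9 leaves detail to a SAP whose text is not in the documents available, so the point may be settled there; the protocol definition still needs correcting.

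**Three stronger readings are tempting but not supported.**

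- A reader might infer that the PP cure rate is close to 100% by construction. That needs s near 0. Failures first found at Day 28 meet the Day 28 condition, and the evaluable-PCR clause presupposes that some parasitaemic children remain. Over the assumed range the rate is about 96% to 98.5%.
- A reader might take the 30% to 98% as the risk of a false trial claim. It is not: mITT counts every withdrawal except loss to follow-up as a failure, and must also pass.
- A reader might infer that nothing else guards the 90% judgement. The synopsis requires a point estimate above 0.90 for DHA+PPQ in both mITT and PP, and section 9.2.2 adds robustness analyses in the ITT population. The guard is partial: the synopsis rule covers only the test arm, and no decision rule is attached to the robustness analyses.

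**Conclusion.** The point holds as a contradiction within the plan. As written, the PP definition excludes most children who fail or recur before Day 28, while the plan's PP cure rate, PP power and PP failure-rate analysis all require them. The direction of the bias is certain: cure rates go up and the difference moves towards zero. Its size depends on s, which is assumed, and the headline figures leave re-infections in.

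Type I error for the trial claim stays below 2.5% in every scenario examined. The damage is that the two-population requirement becomes, in effect, an mITT-only test, and that the 90% judgement as placed in section 9.2.2 cannot be trusted. Because this concerns a co-primary population and is settled by wording alone, it should be corrected before any unblinded analysis.

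**What to change.** In section 9.1:

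- Include in PP any otherwise eligible child who has the Day 28 assessment, or who met the criteria for early treatment failure, late clinical failure or recurrent parasitaemia before Day 28, with an evaluable PCR required for late recurrences.
- Apply the Day 28, missed-visit and other-antimalarial conditions only up to the day of failure or recurrence.
- State that rescue therapy given for a failure or recurrence is not a reason for exclusion.

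In section 9.2.2, state that failures are events on the day they occur. How re-infections enter the Kaplan-Meier analysis is a separate estimand choice, since sections 2.1 and 9.2.1 count them as successes, and this edit need not change it.

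Reconcile section 4.4 (no study investigations after clinical failure) with section 5 (safety follow-up to Day 42). Carry the same PP wording into the SAP.

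The cost is protocol and SAP wording only, with no new data or patients. The PP cure rate will be lower than under the literal rule, and the population will be the one on which the 82% power was computed.
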